### Measurements

See Table 2 for an outline of measurements taken at each data collection time point.

**Table 2 Tab2:** BRIDGE-CRC trial measurements

Data type	Baseline	Month 3	Month 6
*Anthropometrics*			
Height	X		
Weight^a^	X	X	X
Body composition (DXA)	X		X
*Inflammatory markers*			
Systemic inflammation (hs-CRP)	X	X	X
Circulating cytokines (GM-CSF, IL-2, IL-4, IL-6, IL-8, IL-10, TNFα, and IFNγ)	X	X	X
*Metabolic risk*			
Glucose, mg/dL	X	X	X
Insulin, uIU/mL	X	X	X
Hemoglobin A1c, %	X	X	X
HOMA-IR (calculated from glucose and insulin)	X	X	X
Blood pressure, mmHg	X		X
*Dietary intake*			
VioScreen food frequency questionnaire (FFQ)	X		X
24-h diet recall (two per timepoint) (ASA24)	X	X	X
MEPA-III MedDiet screener	X	X	X
Medication use	X	X	X
Physical activity (steps per day, FitBit)	X		X
Microbiota composition (16S rRNA)	X	X	X
Predicted gene abundance, metabolic pathways, and microbial network analysis	X	X	X
Quantification of the following genes via PCR: *dissimilatory sulfite reductase A* (pan*dsrA*), *B. wadsworthia*-specific *dsrA*, *16S rRNA*, *Desulfovibrio* spp.-specific *16S rRNA*, BA *7α-dehydratase* from *C. scindens*, *butyryl-CoA transferase* gene (*BcoA*)	X	X	X
Fecal short chain fatty acids (uM) (e.g., butyrate, acetate, and propionate)	X	X	X
Fecal and circulating bile acids (uM) (i.e., total BAs, total unconjugated BAs, taurine- and glycine-conjugated BAs, and CA, CDCA, LCA, and DCA)	X	X	X
Exfoliated intestinal cell gene expression analysis	X	X	X
Surveys			
Demographics	X		
Health history, including bowel health	X		X
Sleep quality	X		X
Food away from home	X		X
*Psychosocial variables*			
Discrimination	X		
Food security	X		X
Depressive symptoms	X		X
Stress	X		X
Recent trauma	X		X
Anxiety	X		X

*Abbreviations: BA* bile acid, *CA* cholic acid, *CDCA* chenodeoxycholic acid, *DCA* deoxycholic acid, *DXA* dual energy X-ray absorptiometry, *GM-CSF* granulocyte-macrophage colony-stimulating factor, *HOMA-IR* Homeostatic Model Assessment for Insulin Resistance, *hs-CRP* high-sensitivity C-reactive protein, *IFN* interferon, *IL* interleukin, *LCA* lithocholic acid, *MedDiet* Mediterranean diet, *MEPA* Mediterranean Eating Pattern for Americans, *TNF* tumor necrosis factor

^a^Weight will also be recorded as needed throughout the intervention to monitor compliance

### Anthropometrics

Height will be measured, in duplicate, to the nearest 0.1 cm at the beginning of the study using a fixed stadiometer (Seca, Birmingham, UK). Weight will be measured, in duplicate, to the nearest 0.1 kg using a digital scale (Tanita, Arlington Heights, IL, USA). Body composition will be measured with dual energy X-ray absorptiometry (DXA) on a General Electric Lunar iDXA machine (GE Healthcare, Chicago, IL, USA).

### Blood-based biomarkers

Participants, who have fasted for at least 12 h, will undergo a blood draw, and we will retain whole blood and derive serum, plasma, and buffy coat using centrifugation at 3000 RPM for 15 min at 4°C. Blood products will be sent to Quest Diagnostics (Wood Dale, IL, USA) immediately or stored in a −80°C freezer for later analysis.

### Inflammatory markers

Systemic inflammation will be operationalized with CRP and measured with an immunoturbidimetric assay at Quest Diagnostics (Wood Dale, IL, USA). Circulating cytokines (GM-CSF, IL-2, IL-4, IL-6, IL-8, IL-10, TNFα, and IFNγ) will be measured with the Bio-Plex human cytokine assay (Bio-Rad, Hercules, CA, USA) at the UIC Research Resources Center (Chicago, IL, USA).

### Metabolic risk

Glucose, insulin, and HbA1c will be measured by Quest Diagnostics (Wood Dale, IL, USA) using spectrophotometry, an immunoassay, and an enzymatic assay, respectively. Homeostatic model assessment of insulin resistance (HOMA-IR) will be calculated according to a published formula: (fasting glucose [mmol/l]×fasting insulin [μU/ml])/22.5 [35].

### Blood pressure

Blood pressure will be measured with an electronic, automated blood pressure machine (Omron 3 Series, Kyoto, Japan). Participants will rest for a minimum of 5 min before having their blood pressure measured twice in a seated position. Participants will be instructed to rest for 1 min between the two blood pressure readings.

### Dietary intake

Habitual diet will be assessed with the validated, online, VioScreen food frequency questionnaire (FFQ) [36]. Recent dietary habits will be collected and analyzed using the Automated Self-Administered 24-hour (ASA24) Dietary Assessment Tool, version (2020), developed by the National Cancer Institute, Bethesda, MD, USA [37]. The ASA24 will be completed twice at each data collection point. While both instruments are designed to be self-administered, they will instead be administered by trained and certified research staff to reduce recall bias. A MedDiet adherence score first created by Panagiotakos et al. [38] and later adapted to an American population by Tangney et al. [39] will be calculated from both the FFQ and ASA24 data. Lastly, the MEPA-III MedDiet screener [25], developed by Tangney et al., will be used not only as a screener but to quickly assess MedDiet adherence at each data collection timepoint for the Med-A and WL-Med arms. It consists of 21 items divided into 9 categories (e.g., fruits, vegetables, nuts and seeds) and assesses frequency and quantity of intake of foods encouraged and discouraged by a MedDiet eating pattern.

### Medication use

We will catalog prescription medications, over the counter drugs, and dietary supplements taken in the past 30 days.

### Physical activity

Participants will wear a fitness tracker (FitBit, San Francisco, CA, USA) for 7 days. We will access steps, heart rate, and sleep data from the FitBit with a third-party application, FitaBase (San Diego, CA, USA).

### Stool collection

Stool will be collected by participants 0–48 h prior to each of the three data collection visits using a kit provided by study staff. They will be instructed to store collected stool in a commercial refrigerator and to transport the stool on an ice pack to each visit. The stool will be stored in a refrigerator during the study visit. After the visit, it will be processed immediately for exfoliomics analysis (see below), with the remaining stool being aliquoted, flash frozen in liquid nitrogen, and then stored at −80°C until further analysis.

### Fecal microbiota composition

Microbial DNA will be extracted with the Qiagen DNeasy PowerLyzer Powersoil Kit (Qiagen, Hilden, Germany) as done previously [7]. The UIC Genomics core will polymerase chain reaction (PCR) amplify genomic DNA with primers CS1_515F and CS2_806R (modified from the set used by the Earth Microbiome Project) targeting the V4 region of microbial small subunit ribosomal RNA (rRNA) genes. Amplicons will be generated using a two-stage PCR protocol, described previously [40, 41]. The V4 region of the 16S rRNA gene will be sequenced with the Illumina MiSeq platform to generate 2×250 bp paired end reads per sample [42]. Environmental controls will be included in the sequences to distinguish from any contaminants in reagents or the lab environment.

### Fecal microbiome analysis

16S rRNA reads will be processed with DADA2 [43]. After quality filtering and removing low abundance (<0.5%) reads, Silva v132 reference sequence database [44] will be used for taxonomical assignment of the Amplicon Sequence Variants (ASVs).

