## Introduction

Colorectal cancer (CRC) is the third most common cancer in the USA, with 151,030 new cases and 52,580 CRC-related deaths expected in 2022 [1]. Among all racial/ethnic groups, people who identify as African American/Blacks (AA/Bs) have the second highest CRC incidence and highest CRC mortality in the USA [1]. This disparity may exist in part because AA/Bs, compared to other racial/ethnic groups, have a higher prevalence of risk factors for CRC, such as higher body fatness [2, 3], lower dietary fiber consumption [3, 4], poorer diet quality [5, 6], and higher intake of saturated fats [7, 8] and animal proteins [3, 8, 9].

While there are several proposed mechanisms linking these modifiable risk factors with CRC, one potential mechanism is the bile acid (BA)-gut microbiome axis [10–12]. This is the two-way interaction between the gut microbiome and BAs that may explain the etiology of several diseases [13]. High levels of dietary fat and animal protein increase fecal and circulating BAs and promote a shift in amino acid conjugation of the BA pool from glycine to taurine [14, 15]. The gut bacteria *Bilophila wadsworthia* and *Clostridium scindens* can increase their abundance from, and metabolize taurine-conjugated BAs to increase fecal levels of the tumor-promoting/secondary bile acid deoxycholic acid (DCA) and to increase concentrations of hydrogen sulfide (H_2_S), a carcinogen that can trigger dysregulated cell-cycle progression and DNA repair responses [12]. Importantly, *B. wadsworthia* is significantly more abundant in uninvolved mucosa of CRC cases versus controls among AA/Bs but not non-Hispanic Whites [7]. Furthermore, H_2_S dampens production of butyrate [16], an anti-neoplastic microbial metabolite [17]. Hence, the gut microbiota may explain to some extent why higher intakes of fat and animal protein sometimes observed in AA/Bs compared to other race/ethnicities place them at increased risk of CRC.

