### Statistical analysis of the 16S rRNA data and predicted microbial metabolic pathways

ASV counts will be normalized using cumulative sum scaling [68]. Differences in community richness, evenness, and structure [alpha (i.e., Shannon index) and beta diversity (i.e., Unifrac [69] and Bray-Curtis distances)] between groups will be determined using PERMANOVA from vegan R package. Generalized linear mixed models (GLMMs) will determine the phenotypic variables, cardiometabolic outcomes, and BA-associated variables associated with each microbial ASV and genus level as implemented in MasLin [70], with treatment group as the main fixed factor, adjusting for important covariates, such as age and medication usage. Multiple comparisons will be adjusted using false discovery rate (FDR) [71]. An FDR-corrected *p*-value ≤ 0.001 will be deemed significant. All analyses will be done with R using functions encoded in the phyloseq package [72]. ASVs will be employed to determine the most likely associated microbial genes that encode for enzymes and associated microbial metabolic pathways using PiCRUSt2 [45]. GLMMs will be employed to determine the genes and metabolic pathways associated with each intervention arm with MasLin [70]. Finally, we will determine the likelihood that the ensemble of microbial genes associated with the production and consumption of DCA and H_2_S are affected by the interventions.

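### A 0.5% abundance cut with no stated denominator appears to precede the diversity and ASV analyses; read per sample or pooled, it caps retained ASVs at 200 and can distort richness

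*Protocol article*

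**What the plan says.** Under Fecal microbiome analysis, reads go through DADA2, and the text continues: "After quality filtering and removing low abundance (<0.5%) reads", the Silva database serves to assign taxonomy to the ASVs. The threshold is a number, but its denominator is not given. It could be the share of one sample, the share of all reads in the study, or a level to be reached in at least one sample.

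The section on statistical analysis of the 16S data starts from ASV counts, normalised by cumulative sum scaling. It compares "Differences in community richness, evenness, and structure [alpha (i.e., Shannon index) and beta diversity (i.e., Unifrac [69] and Bray-Curtis distances)] between groups" and models each ASV and genus. It then states that "ASVs will be employed to determine the most likely associated microbial genes that encode for enzymes and associated microbial metabolic pathways using PiCRUSt2", and finally asks whether the genes for producing and consuming deoxycholic acid and hydrogen sulfide respond to the interventions. ASVs are also a feature class in the linear discriminant search and in the sparse canonical correlation analysis. No section describes a second, unfiltered table.

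The Introduction rests the mechanism on two bacteria that "can increase their abundance from, and metabolize taurine-conjugated BAs". The section on quantification of microbial gene targets measures, by qPCR, pan-dsrA, the *B. wadsworthia* dsrA, *Desulfovibrio* 16S, *C. scindens* baiE and BcoA. Community structure and composition is a secondary outcome.

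**The concern.** Richness counts taxa, and in an uneven community most taxa are rare. A filter that deletes taxa by abundance therefore removes much of what richness is meant to count. What is left is the number of taxa above a line. That number depends on how evenly reads are spread as well as on how many taxa are present. A diet that adds minor taxa need not raise it, and could lower it.

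The same applies to individual ASVs under a per-sample rule. A taxon near the line turns into zeros in many samples and contributes no predicted genes there. At stake is a named secondary outcome and the PiCRUSt2, network and integration analyses that share its input.

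**Working it through.** The plan gives no derivation of the 0.5%, so there is no figure to reproduce. From the article come the threshold (0.005), its position before taxonomic assignment, and 192 participants at three visits (192 × 3 = 576 samples). Community size, evenness and read depth are not given. They are assumed below and varied.

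**1. Arithmetic cap.** Relative abundances sum to 1, so the number of ASVs holding at least a share *t* is at most 1/*t*.
- *t* = 0.5%: 1/0.005 = 200
- *t* = 0.05%: 1/0.0005 = 2,000
- *t* = 0.005%: 1/0.00005 = 20,000

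The 200 applies to each sample under a per-sample rule and to the whole study under a pooled rule.

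**2. Per-sample cut in assumed communities.** ASV abundances were lognormal and 30,000 reads were drawn multinomially, with 200 replicates per setting. ASVs below 0.5% of the sample were dropped. Mean number of ASVs kept:

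| True ASVs | log-SD 1.0 | 1.5 | 2.0 | 2.5 |
|---|---|---|---|---|
| 100 | 58 | 40 | 28 | 21 |
| 200 | 62 | 47 | 33 | 25 |
| 300 | 55 | 48 | 36 | 28 |
| 500 | 40 | 45 | 39 | 31 |

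Across the grid, 21 to 62 ASVs survive, which is 8% to 58% of those observed. Between 7% and 66% of reads are dropped, and Shannon falls by 0.33 (2.54 to 2.21) to 2.14 (5.71 to 3.57). A 0.005% cut would keep 83% to 100% of ASVs and change Shannon by at most about 0.02.

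**3. Does filtered richness follow unfiltered richness?** In three uneven communities (150 ASVs with log-SD 1.8; 250 and 400 with log-SD 2.0), observed richness of 147, 232 and 359 becomes about 36, 36 and 38. When true richness varies from 100 to 500 at log-SD 2, the correlation between filtered and unfiltered richness is only about 0.3. At log-SD 1.0 the order reverses:

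| True ASVs | Filtered richness | Unfiltered Shannon | Filtered Shannon |
|---|---|---|---|
| 200 | 62 | 4.80 | 3.93 |
| 300 | 55 | 5.20 | 3.86 |
| 500 | 40 | 5.71 | 3.57 |

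**4. One ASV under a per-sample rule.** With geometric mean *m* and an assumed between-sample log-SD of 1.0, the share of samples in which it survives is 1 − Φ(ln(0.005/*m*)).
- *m* = 0.1%: 1 − Φ(1.61) = about 5%
- *m* = 0.2%: 1 − Φ(0.92) = about 18%
- *m* = 0.5%: 50%; after a true halving, 1 − Φ(0.69) = about 24%

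**5. The lenient reading.** Suppose an ASV is kept throughout if it reaches 0.5% in at least one of the 576 samples. With the three communities of step 3 and an assumed between-sample log-SD of 0.7 to 1.5, roughly 100 to 370 ASVs are kept, 0% to 6% of reads are lost and Shannon falls by about 0.25 at most. The cap of 200 does not apply under this reading.

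**The case against.** The article is a condensed account. It places the cut before taxonomic assignment but never says that the filtered table feeds the diversity measures, and Shannon, UniFrac and Bray-Curtis need no taxonomy. This stands: the link is inferred from the order of the text and from the absence of any other table. It is still the natural reading, and if another table or threshold is meant, the wording needs correcting anyway.

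The named alpha-diversity index is Shannon, and in the three uneven communities filtered and unfiltered Shannon correlate at about 0.98 to 0.99. Most of the fall there is a shift in level that would largely cancel between arms. This also stands. A reader might infer that every diversity comparison is invalid, and the calculations do not show that. The article does, however, list richness as a target, and the ordering of Shannon can fail when true richness differs in even communities.

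A reader might also infer that the trial loses the organisms it is about. The documents do not support this. They give no relative abundance for *B. wadsworthia*, *C. scindens* or *Desulfovibrio*, and the qPCR targets cover all three whatever the 16S filter does. What could be weakened, if these organisms lie below 0.5%, is their 16S, network and PiCRUSt2 readout and their part in the feature-selection and integration analyses.

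**Conclusion.** The point holds in a limited form. As written, the plan applies a 0.5% cut with an undefined denominator ahead of the only ASV table described. Under a per-sample or pooled reading at most 200 ASVs survive. In the assumed communities a per-sample cut leaves about 21 to 62, so richness no longer measures what its name says. In even communities Shannon can be misordered too. If the rule is that one sample must reach 0.5%, the effect is small.

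Only the cap follows from the plan's own figure. The other sizes depend on assumed community shape, 30,000 reads and, in steps 4 and 5, an assumed between-sample spread. No intervention effect on trial data was modelled, so a specific loss of power is not claimed. The outcomes affected are secondary or exploratory. The bile acid primary outcomes and the qPCR results are untouched. The change is worth making because the possible bias falls on a named secondary outcome and can be removed on the same sequencing data.

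**What to change.** - State what the 0.5% is a percentage of, and confirm that 0.5% is the intended value.
- Compute richness, evenness, Shannon, UniFrac and Bray-Curtis on the DADA2 table after quality, chimera and contaminant removal but without the 0.5% cut. State how sequencing depth is handled.
- Confine any abundance or prevalence filter to the feature-level analyses (ASV and genus models, PiCRUSt2, linear discriminant analysis, sparse canonical correlation). Set it low enough not to remove minor taxa, and repeat these analyses under another threshold as a sensitivity analysis.

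The particular filter and the method for depth are for the investigators to choose, provided both are fixed before the data are analysed. The cost is wording and some computing on the same sequencing data. The downside is that more features enter the false discovery rate correction, so each feature-level test faces a heavier multiplicity burden.

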### Predicted gene abundance, metabolic pathways, and microbial network analysis

Employing the software PiCRUSt2 [45], we will predict gene abundance and most probable metabolic pathways using ASVs as input. The software SPIEC-EASI will be used to model microbial network configurations [46].

### Quantification of microbial gene targets

Quantitative PCR (qPCR) will be performed with a 7500Fast Real-Time PCR system (Life Technologies, Carlsbad, CA, USA) and validated primers, as described previously [7, 8, 47], using microbial DNA isolated as explained above. Functional gene targets for sulfide production will be measured including degenerate dissimilatory sulfite reductase A (pan-dsrA) and *B. wadsworthia*-specific dsrA (dsrA-Bw). Primers targeting 16S rRNA genes will be used to measure total bacterial abundance as well as *Desulfovibrio* spp. The BA 7α-dehydratase (*baiE*) gene from DCA producing *C. scindens*, and *butyryl-CoA transferase* gene (*BcoA*) will also be quantified. An internal standard will be used.

### Fecal SCFAs

Flash frozen stool will be transferred into plastic tubes; 2,2-dimethylbutyric acid will be added at 1 mmol/L as internal standard, vortexed and centrifuged, and supernatant filtered through a Millex-GS filter (Millipore, Burlington, MA, USA) and refiltered with a microconcentrator (Millipore, Burlington, MA, USA). The final filtrate will be analyzed using an Agilent Technologies 6890N Network GC System (Santa Clara, CA, USA) with a flame ionization detector for SCFAs. A mixed-SCFA standard solution will be prepared using high purity (0.99%) reagents (Sigma, St. Louis, MO, USA). Fecal SCFA concentrations will be computed by using a peak area ratio of the sample profile relative to the internal standard. Analysis will be conducted by the UIC Mass Spectrometry, Metabolomics and Proteomics Facility.

### Fecal and circulating bile acids

All major primary (e.g., CA and CDCA) and secondary fecal and circulating BAs (e.g., DCA and LCA) as well as their glycine and taurine conjugates will be assessed. Total BAs and total unconjugated BAs will also be measured. Samples will be extracted, and supernatants will be dried and resuspended for liquid chromatography/mass spectroscopy analysis following validated and published methods [48]. Authentic reference BAs will be purchased from Sigma-Aldrich (St. Louis, MO, USA) and Steraloids (Newport, RI, USA). Blind duplicate samples will be used to assess inter- and intra-batch variability. An internal standard will be used.

### Stool-based exfoliated intestinal epithelial cell analysis—exfoliomics

From stool preserved in Ambion Denaturation Solution, eukaryotic polyA+ RNA will be isolated using the Active Motif mTRAP Maxi kit followed by DNA removal with DNAFree (Invitrogen, Waltham, MA, USA) as previously described [49]. Illumina libraries will be created with 100 ng RNA using the Lexogen QuantSeq 3′ mRNA-Seq Library Prep Kit for Illumina (FWD) (Lexogen, Vienna, Austria) and unique molecular identifiers. The libraries will be generated following the adjusted protocol from the manufacturer for low input RNA and quantified using the Qubit 1x dsDNA HS assay kit (ThermoFisher Scientific, Waltham, MA, USA) and a Bioanalyzer High Sensitivity DNA Analysis kit (Agilent, Santa Clara, CA) following manufacturer’s instructions. Sequencing will be performed on an Illumina NovaSeq 6000 platform using standard Illumina protocols. RNA reads will be mapped with the Bowtie2 [50] using optimized parameters to the Ensembl GRCh38 human reference. Reads will be examined for quality control using FastQC and quantified using HTSeq-count [51, 52]. Sequencing reads will be filtered to remove any gene with less than 2 reads in more than 33% of the samples [49].

### Surveys

All non-dietary surveys will be electronic and self-administered. The measures include demographics (e.g., sex, household income), health history including bowel health (Bowel Health Questionnaire from NHANES [53]), sleep quality (Pittsburgh Sleep Quality Index [54]), discrimination (Everyday Discrimination Scale [55]), food security (US Household Food Security Survey Module [56]), depressive symptoms (Patient Health Questionnaire-8 (PHQ-8) [57]), perceived stress (Perceived Stress Scale (PSS-10) [58]), recent trauma (Recent Traumatic Events Scale [59]), anxiety (Generalized Anxiety Disorder scale, GAD-7 [60]), and food (eaten) away from home [61].

## Statistical analysis plan

### Sample size

We calculated the sample size to detect group differences in three circulating and fecal BA outcomes (total BAs, taurine-conjugated BAs, and DCA) using results reported by Biemann et al. [19] and Aleman et al. [18] as a guide. In Biemann et al. [19], data were summarized as medians, interquartile ranges, and sample sizes; we estimated the corresponding means and standard deviations [62]. Estimated effect sizes for diet intervention on serum total BAs and taurine-conjugated BAs are 0.75 and 1.2 (assuming the correlation coefficient between pre and post measurements is 0.9 as commonly observed in repeated assays). Estimated effect size on fecal DCA is 0.67 using the raw data provided by Aleman (assuming change in the control group is 0) [18, 62]. For each dependent variable, the overall level of type I error is set at *α* = 0.05; that is, no adjustment is made for correlation among dependent variables and hence tests of these variables are not independent. The sets of variables examined in Hypotheses 1 and 2 should be interpreted as related. With 4 groups, there are 6 pairwise contrasts among cell means at a given occasion; we plan to test 3 of these using *t*-tests at the Bonferroni-adjusted *α*^′^ = 0.05/3 ≈ 0.017 significance level. For the smallest effect size 0.67, we need 41 subjects per group to afford power of 0.80 at *α*^′^ = 0.017. Note that in all cases these are one-sided tests of superiority in that change in one group’s mean is hypothesized to be greater than change in that of another group [63, 64]. For the smallest effect size, we need 164 subjects to complete the study, which offers ample power for the other effect sizes. Assuming 15% dropout at 6 months based on our previous studies, the recruitment target is 192 subjects (48 per arm).

Normal continuous variables will be presented as mean ± standard deviation. Continuous variables which cannot be transformed to achieve normality will be presented as median (interquartile range). Discrete variables will be presented as percentages.

Statistical analysis will be conducted using SAS v9.4 (Cary, NC). Independent and dependent *t*-tests will be employed to investigate differences in outcome measures between and within study groups, respectively. Any non-normal variables which cannot be transformed will be analyzed with the Mann-Whitney *U* and Wilcoxon signed-rank tests. The effect of the interventions on change in primary outcomes at mid- and post-intervention will be examined using repeated-measures linear models with restricted maximum likelihood estimation and a fully specified covariance matrix in SAS [65–67]. Such modeling can handle missing data as long as the data is missing at random, making this method ideal for our intention-to-treat analysis. Baseline covariates including the stratification variables for randomization will be adjusted for in all models. We will determine Spearman’s rank correlations between changes in circulating and fecal BAs and changes in fasting glucose, insulin, HOMA-IR, and circulating pro-inflammatory cytokines. We will also determine partial correlations for the above by adjusting for pertinent covariates, such as BMI.

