The gut microbiota may also help explain how weight loss (WL), increased fiber, and decreased fat and animal protein consumption may decrease CRC risk in this subgroup. Aleman et al. demonstrated that a VLCD producing 10% WL reduced fecal BAs and DCA, and yielded a higher ratio of glycine-conjugated BAs, which correlated directly with gut microbial compositional changes [18]. Biemann et al. showed that a 5–15% WL from a lifestyle intervention significantly reduced circulating BA levels compared to a control group [19]. Lastly, in O’Keefe et al., increasing fiber consumption and decreasing saturated fat and animal protein in in AA/Bs for 2 weeks increased fecal butyrate and reduced *B. wadsworthia* abundance, fecal DCA levels, and colonic histological biomarkers of CRC [8].

Based on these prior studies, we hypothesize that the largely plant-based and fiber-rich Mediterranean diet (MedDiet), which is associated with lower circulating DCA [20], higher abundance of fecal bacteria capable of producing butyrate [21], and decreased CRC risk in observational studies [22], will have robust positive effects on the BA-gut microbiome axis among persons with elevated levels of colonic bacteria capable of producing sulfide, including AA/Bs. Furthermore, because weight loss and a healthful diet may have an additive effect on disease risk reduction [23], we hypothesize that WL via caloric restriction combined with a MedDiet will induce the greatest weight loss, the greatest improvements in the microbiome-BA axis, and the greatest reduction in intestinal gene expression associated with carcinogenesis.

To our knowledge, no studies have tested this hypothesis. To fill this gap, we will conduct a randomized controlled trial (RCT) enrolling AA/B, middle to older aged adults with obesity to examine the effects of a MedDiet alone (Med-A), WL through lifestyle intervention alone (WL-A), or a calorie-restricted MedDiet for WL (WL-Med) compared to typical diet controls (TDC), on BA metabolism, the gut microbiota, and intestinal epithelial markers associated with carcinogenesis.

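### Holm's step-down test would add power to the three planned contrasts per outcome at the same familywise 0.05 and no extra participants; single-step Bonferroni is valid but less efficient

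*Protocol article*

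**What the plan says.** All of this stands in the Sample size section of the protocol article.

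- Error rate: "For each dependent variable, the overall level of type I error is set at *α* = 0.05". The section states that nothing is adjusted across outcomes.
- Contrasts: of the six pairwise comparisons among four arms, "we plan to test 3 of these using *t*-tests at the Bonferroni-adjusted" level, given as "Bonferroni-adjusted *α*^′^ = 0.05/3 ≈ 0.017 significance level". The three are not named.
- Direction: "Note that in all cases these are one-sided tests of superiority".
- Sizing: "For the smallest effect size 0.67, we need 41 subjects per group to afford power of 0.80 at *α*^′^ = 0.017". Across four arms, "we need 164 subjects to complete the study, which offers ample power for the other effect sizes".

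No step-down, gatekeeping or other sequential rule for these contrasts appears in the article. The false discovery rate adjustments described later concern the microbiome and gene-expression data only.

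**The concern.** Single-step Bonferroni holds each contrast to 0.05/3 whatever the other two show. Once one contrast has been declared at 0.05/3, at most two true nulls can remain, so the rest can be tested at more generous levels without raising the familywise error. Holm does this: the smallest p-value is compared with 0.05/3, the next with 0.05/2 and the largest with 0.05, stopping at the first failure.

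This works for any three contrasts and any correlation between them, including contrasts that share an arm, so it does not depend on which three are meant. It also applies whether the p-values come from t-tests or from the repeated-measures models described later in the analysis plan. What is at stake is power at a fixed sample size, for each outcome on which more than one contrast is truly non-null. The validity of the planned test is not in question.

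**Working it through.** **Inputs from the Sample size section.** Familywise α = 0.05 per outcome; three contrasts; one-sided; smallest standardized effect d = 0.67; n = 41 completers per arm.

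**Reproducing the plan's figure.** For a two-sample t-test with n per arm, df = 2n − 2 and the noncentrality parameter is d·√(n/2).

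- n = 41: df = 80; noncentrality 0.67 × √20.5 = 3.034; one-sided critical value at 0.05/3 is 2.165; power = 0.806. At the rounded 0.017, power is 0.808.
- n = 40: power = 0.795.

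So 41 is the smallest n that reaches 0.80, and the plan's figure is confirmed.

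**What the later Holm steps offer.** The same calculation at n = 41 and d = 0.67 gives power 0.850 at one-sided 0.025 and 0.914 at one-sided 0.05. Under Holm, the power of a 0.67 contrast lies between 0.806 and 0.914, depending on how often the other contrasts are rejected first.

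**Simulation.** Four arms, 41 completers each, normal data with equal variances, one-sided two-sample t-tests, 400,000 trials per pattern (Monte Carlo error about 0.001). The contrast sets (each active arm against TDC; WL-Med against each other arm) and the true effects are assumptions. Where both contrast sets were run for a pattern, they gave the same results to within about 0.002.

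| True effects of the three contrasts | Power for a 0.67 contrast: Bonferroni → Holm | All three declared: Bonferroni → Holm |
|---|---|---|
| 0.67 / 0.67 / 0.67 | 0.806 → 0.876 | 0.62 → 0.79 |
| 0.67 / 0.67 / 1.34 | 0.806 → 0.894 | 0.70 → 0.85 |
| 0 / 0.67 / 0.67 | 0.806 → 0.836 | not applicable |
| 0.335 / 0.335 / 0.67 | 0.806 → about 0.815 | 0.13 → 0.26 |
| 0 / 0 / 0.67 | 0.806 → 0.806 | not applicable |

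In the fourth row the two 0.335 contrasts rise from 0.26 to 0.36.

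**At least one rejection.** This is identical under both rules, because Holm's first step is the Bonferroni test. For example, it is 0.952 for both in the first row.

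**Error control.** With all three nulls true, familywise error is about 0.043 for both rules. With one real contrast it is 0.031 (Bonferroni) and 0.045 (Holm). With two real it is 0.017 and 0.049. Holm stays within 0.05 throughout.

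**Equivalent in participants.** To reach about 0.875 for a single 0.67 contrast at 0.05/3, Bonferroni needs 49 completers per arm, eight more than planned.

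**The case against.** The strongest reply is that nothing here is wrong. Bonferroni is valid, keeps the declared 0.05, agrees with the sample size calculation and delivers the promised power. That stands in full, and it limits this point to an improvement.

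The gain also depends on effects nobody knows and contrasts the article does not name. It is small when the single-component arms have half the combined effect, and nil when only one contrast is real. That stands too, and is why the size is given as a range.

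Third, Holm has a price. With all three effects at 0.67, about 19% of trials have at least one contrast that Holm declares and Bonferroni does not; its Bonferroni-width simultaneous interval includes zero. Bonferroni also bounds the expected number of false rejections per outcome at 0.05, and Holm does not. With one real contrast, the two null contrasts are each rejected with probability about 0.0275, so the expected number is 2 × 0.0275 = 0.055. A team that makes no adjustment across outcomes might prefer the stricter rule for that reason. But the error rate the plan declares is the overall one per outcome, and Holm controls that.

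Some stronger readings are tempting, and the document does not support them:

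- **The central hypothesis needs several contrasts to succeed together.** The Introduction expects the combined arm to give "the greatest improvements in the microbiome-BA axis, and the greatest reduction in intestinal gene expression associated with carcinogenesis", but the plan states no rule that all contrasts must succeed. If the three are each active arm against TDC, they do not compare the combined arm with the single-component arms at all. If all three did have to succeed, each could be tested at the full 0.05, and Holm would not be the natural remedy.
- **The trial has no slack.** The 41 are completers for the smallest effect. For the other two effect sizes the same test has power 0.889 (d = 0.75) and above 0.999 (d = 1.2). The primary outcomes are also to be analysed with repeated-measures models that use incomplete data and adjust for baseline covariates.
- **The effects 0.67, 0.75 and 1.2 are three contrasts in one family.** They belong to three different outcomes (fecal DCA, serum total bile acids and serum taurine-conjugated bile acids). Neither correction acts across outcomes, so they say nothing about Holm's gain.
- **The sample size could be cut.** With all three effects at 0.67, Holm reaches 0.80 per contrast at about 34 per arm. If only one contrast is real, power at 34 is only about 0.72.

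**Conclusion.** The point holds as a cheap gain in efficiency. At the planned 41 completers per arm, Holm raises power for a 0.67 contrast from 0.806 to between about 0.815 and 0.894 in the patterns examined with two or three non-null contrasts. It leaves power unchanged when only one contrast is real, and never lowers it. The probability of at least one rejection is the same under both rules.

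That Holm rejects at least as much at the same familywise error is a mathematical property and needs no assumption about the contrasts or their correlation. The size of the gain rests on the assumed contrast sets and effects, equal variances, and 41 completers in every arm. Neither the sample size nor the validity of the planned tests is affected.

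**What to change.** Before any outcome data by arm are seen, replace the fixed 0.05/3 rule in the analysis plan with a sentence such as: within each dependent variable, the three planned one-sided contrasts will be tested by Holm's step-down procedure at a familywise error rate of 0.05, with ordered p-values compared with 0.05/3, 0.05/2 and 0.05, stopping at the first non-rejection.

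Keep the sample size calculation as it is: 41 completers per arm, with 0.80 as the minimum power for any one contrast at 0.67. Say also how intervals will be reported, for instance at Bonferroni width, with a note that a contrast declared by Holm may have an interval that includes zero.

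The cost is one sentence of wording, no additional participants, and the loss of simple simultaneous intervals that match the tests. If outcomes by arm have already been seen, the planned Bonferroni rule should stand.
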